### Sample Size Calculation

A sample of 29 health records of previously treated patients with melanoma who experienced IrAEs was used to estimate the required sample size. Patients with lung cancer were not considered for this calculation due to the lack of accessibility to symptomatic IrAE data in that population. Only records where the symptom onset was reported were included for this sample size calculation. In that record sample, the time interval between symptom onset and clinician detection of symptomatic IrAEs was estimated at 4.43 days, with an SD of 3.65 days. A 2-sample *t* test with a statistical power of 90% and significance level set at .05 determined that 138 participants would be required to detect a 2-day difference, assuming the same SD of 3.65 days. Given that similar studies have reported an attrition rate of 30%, the target sample size was adjusted to 198 patients [36,50].

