## Introduction

Immune checkpoint inhibitors (ICIs) have increasingly become part of the standard treatment for multiple cancer types and stages, with the main benefits including superior overall survival rates [1-14]. Although ICIs are generally considered as well-tolerated, they may trigger immune-related adverse events (IrAEs), which can be severe and result in debilitating or fatal outcomes [15,16]. Treatment modality, cancer type, and patient characteristics appear to influence the likelihood of symptomatic IrAEs, which generally occur in 40%-80% of patients [10,15]. Combinations of ICI agents generally result in a higher incidence and severity of symptoms, with 55% of IrAEs being severe (grade 3 or higher) [15,17]. Even though the incidence of IrAEs appears to be positively correlated with superior objective response rates to ICIs, the occurrence of severe events may lower overall survival rates [2,18]. It is posited that solid tumors that exhibit high mutational burden elicit a stronger immune response, which may trigger more IrAEs [19,20]. Limited evidence suggests that skin, respiratory, renal, and hepatic IrAEs also appear to be correlated with melanoma, lung cancer, kidney cancer, and hepatocellular cancers, respectively, suggesting that different tumor types may increase the likelihood of specific IrAEs [21-23]. In addition, genetic risk factors such as allelic variations of *HLA-B* and mutations in the *TMEM162* gene are correlated with higher or lower likelihood of IrAEs [24]. Recent studies have highlighted that the potential chronicity of IrAEs could further burden patients and contribute to lower overall quality of life [16,25-27]. The timing of detection and intervention of IrAEs appears to play a key role in limiting their progression and outcome [10,15,28].

Although most IrAEs occur within the first 3-6 months of the start of treatment, some may develop after a year even when treatment has been discontinued [15,29,30]. In addition to the uncertainty of when they may manifest, IrAEs are heterogenous in their symptomatic presentation and are usually related to the affected tissue or organ [15]. Therefore, patients need to be ready to engage in self-care activities to self-monitor and self-manage symptoms they confront outside of the clinical environment during the multiple weeks between treatments [31].

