### Study Design

Prior to randomization, subinvestigators collect demographic, medical history, and active treatment data from eligible consenting patients. Participants are randomized by subinvestigators using a web-based REDCap (Research Electronic Data Capture) form (version 12.4.21) [43]. The form has a randomization table (1 per site) using permuted block 1:1 randomization (block size of 4), independently prepared by the study biostatistician. Initially, the IePRO RCT was open to patients with melanoma and patients with lung cancer exclusively, and randomization was stratified by cancer type. Due to challenges in recruitment and following a protocol amendment in April 2022, this study was open to patients with all cancer types, and the stratification criteria were dropped. Blinding was not possible due to the nature of the intervention. Patients are informed that they will be randomly allocated to 1 of the 2 models of care: the standard model (control group) or the digital model (intervention group). The informed consent form and support documentation for the electronic app used to deliver the PRO questionnaires include these same conventions to further mitigate the adverse effects of the lack of blinding toward participants. Data collection instructions and reminders sent to clinicians caring for participants do not indicate which group the participant belongs to.

Patients in both groups obtain access to an electronic mobile app, which contains weekly questionnaires for HRQoL and self-efficacy to manage symptoms. An information sheet detailing how to navigate the app is also provided. Nurses and subinvestigators are available to assist patients in installing the app, registering and signing into an account, and replying to the baseline questionnaires in-person or over the phone. Patients in the intervention group have access to a symptoms questionnaire that is part of the intervention being tested. Automated reminders via emails or push notifications are sent to patients when a new questionnaire is available. Patients in both groups have the same number of scheduled clinician appointments—usually the same day and frequency of the ICI treatment—and are followed up for up to 6 months of ICI treatment.

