### Statistical Methods

In this RCT, the null hypothesis postulates that there is no difference in the primary end point (delay between symptom onset and detection be clinical team) between the intervention and control groups. The primary outcome will be analyzed comparing groups by means of multivariable regressions, adjusting for cancer type, age, and treatment regimen, against a 1-sided hypothesis. Secondary outcomes will be analyzed using multivariate regression analysis, controlled for cancer type, treatment regimen, and age. All statistical analyses will be presented as effect measure plus 95% CI, using a significance level of 5%. Variations in HRQoL and self-efficacy scores will be assessed by adjusting to baseline measure. Overall survival at 6 months will be controlled for cancer type and stage. All data processing and statistical analyses will be performed in R statistical software (v4.2.2; R Core Team 2023) and Microsoft Excel for Microsoft 365 MSO (version 2302, 2023). In-questionnaire data completeness is compulsory, though potential errors in the app may nevertheless occur. In addition, data such as time points may prove difficult to collect. According to the type and amount of missing data, strategies including imputation methods, deletions, or dismissals will be considered. For the HRQoL and self-efficacy for managing symptoms questionnaires, missing data will be handled according to official guidelines [53,55]. For exploratory outcomes, descriptive statistics will be applied. Qualitative data of semistructured interviews will be analyzed by the subinvestigators. Interviews will be transcribed verbatim and analyzed through thematic analysis.

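### The 138 counts patients with a dated symptomatic IrAE, but the target of 198 allows only for attrition, so the stated 90% power is unsupported over most of the protocol's own 40%-80% incidence range

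*Protocol article*

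**What the plan says.** Under Primary Objective and Primary Outcome, the protocol article defines time to detection as the days from the patient-reported onset of a symptom to the clinical team's detection of the associated IrAE. Eligibility Criteria admits adults starting or restarting checkpoint inhibitors; an IrAE is not a condition of entry. The Introduction refers to "symptomatic IrAEs, which generally occur in 40%-80% of patients".

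Sample Size Calculation takes its planning values from "A sample of 29 health records of previously treated patients with melanoma who experienced IrAEs", and keeps only records in which onset was reported. These give a mean delay of 4.43 days and an SD of 3.65 days. With "statistical power of 90% and significance level set at .05", the calculation "determined that 138 participants would be required to detect a 2-day difference, assuming the same SD of 3.65 days". One inflation follows: "Given that similar studies have reported an attrition rate of 30%, the target sample size was adjusted to 198 patients".

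Statistical Methods analyses the primary outcome by regression "adjusting for cancer type, age, and treatment regimen, against a 1-sided hypothesis", at a 5% level, with effects reported with 95% CIs. It also concedes that time points may be hard to collect.

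**The concern.** A patient who never has a symptomatic IrAE has no onset date, no detection date and so no value of the primary outcome. The planning records contain only patients who do have that value, so the 138 is a count of such patients. The step from 138 to 198 uses its whole margin on attrition. It therefore treats every completer as supplying a delay, which does not fit the 40%-80% incidence given in the same article.

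What is at stake is the trial's headline power statement. If fewer than 138 delays are available, a true 2-day benefit is missed more often than the one time in ten that 90% power implies. A non-significant result read against that figure could then be taken as evidence against the model of care when the trial was simply imprecise.

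**Working it through.** **Inputs.** Difference 2 days, SD 3.65, alpha 0.05, power 90%, attrition 30% and target 198 (Sample Size Calculation); 1:1 allocation (Study Design); incidence 40%-80% (Introduction); one-sided primary test (Statistical Methods).

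**Step 1: reproduce 138.** The normal approximation per arm is n = 2 × (z_alpha + z_beta)² × SD² / difference².
- Two-sided: 2 × (1.960 + 1.282)² × 3.65² / 2² = 69.99, so 70 per arm and 140 in all. The exact t test needs 71 per arm, 142 in all. With 138 patients (69 per arm), exact t-test power is 89.2%.
- One-sided: the t test needs 58 per arm, 116 in all.

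The 138 is therefore a two-sided figure, reproduced to within 3%.

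**Step 2: reproduce 198.** 138 / (1 − 0.30) = 197.1, which becomes 198 (99 per arm). Attrition accounts for the whole increase.

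**Step 3: add incidence.** Analysable patients = 138 completers × incidence: 55.2, 82.8 and 110.4 at 40%, 60% and 80%. With no loss at all, 198 × incidence gives 79.2, 118.8 and 158.4.

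**Step 4: power for 2 days.** Noncentral t with N analysable patients split equally, N − 2 degrees of freedom and noncentrality (2 / 3.65) × √(N / 4). At N = 55.2 the noncentrality is 0.548 × √13.8 = 2.04.

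| Scenario | Incidence | Analysable | Power, two-sided 5% | Power, one-sided 5% | Difference detectable at 90% power, two-sided / one-sided (days) |
|---|---|---|---|---|---|
| 30% attrition | 40% | 55 | 51.5% | 64.2% | 3.24 / 2.91 |
| 30% attrition | 60% | 83 | 69.3% | 79.6% | 2.63 / 2.37 |
| 30% attrition | 80% | 110 | 81.4% | 88.8% | 2.27 / 2.05 |
| No loss | 40% | 79 | 67.3% | 78.0% | not needed |
| No loss | 60% | 119 | 84.2% | 90.7% | not needed |
| No loss | 80% | 158 | 92.9% | 96.3% | not needed |

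**Step 5: what would deliver 90%.**
- Two-sided, no loss: incidence of at least 142 / 198 = 72%.
- One-sided, no loss: at least 116 / 198 = 59%.
- One-sided, 30% attrition: at least 116 / 138.6 = 84%, above the top of the stated range.
- Two-sided, 30% attrition: not reachable, since 142 exceeds the 138 completers.

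**The case against.** The best case for the plan has several parts.

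- **Sidedness.** Statistical Methods tests the primary outcome one-sided. On that basis the loss at 80% incidence with full attrition is only about one point (88.8%). This stands, and both bases must be shown. It does not remove the problem: at 60% and 40% incidence power is still about 10 and 26 points short, and the slack arises because the two sections disagree, not because incidence was planned for.
- **Attrition.** A patient who has a dated IrAE and withdraws later may already have supplied the outcome. Data Collection Methods says collection stops at withdrawal, not that recorded delays are discarded. The 55/83/110 are therefore the pessimistic end and the no-loss rows the optimistic end.
- **The 30% might be meant to cover patients without an IrAE.** The text calls it attrition seen in similar studies. To deliver 138 under that reading, incidence would have to be about 70% (138 / 198) with no dropout at all.
- **Several IrAEs per patient could add data.** Possibly, but the calculation counts participants in a t test, and repeated delays within a patient would be correlated.
- **The 40%-80% is a background figure** with no 6-month window and no match to this case mix. That is fair: it serves as a sensitivity range. It is, however, the only incidence the article gives.
- **Reporting of 95% CIs** will make imprecision visible, which softens the risk of misreading but does not correct the stated power.

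A reader might infer that 90% power is missed whatever happens. The documents do not support that: with little loss and high incidence it is met on either basis. Nor is there an arithmetic slip, since both 138 and 198 reproduce.

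**Conclusion.** The point holds as a fault in a planning assumption behind a stated power. With the plan's own 30% attrition, power for a 2-day difference runs from 51.5% to 81.4% two-sided or 64.2% to 88.8% one-sided across the stated incidence range. Only the one-sided figure at 80% comes close to 90%. Allowing for no loss at all, the range is 67.3% to 92.9% or 78.0% to 96.3%. The truth should lie between these bounds, and the unqualified 90% is unsupported over most of them.

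The figures assume an SD of 3.65 days, one delay per patient, incidence equal in both arms and independent of dropout, and 40%-80% applying within the 6-month follow-up. Missing onset dates would lower every figure. Covariate adjustment might recover some precision, but the article claims none.

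**What to change.** Reword the Sample Size Calculation paragraph along these lines:

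*The 138 refers to patients with at least one symptomatic IrAE with dated onset and detection; it gives about 89% power for a 2-day difference (two-sided 5% t test, SD 3.65). With 198 randomised and symptomatic IrAEs in 40%/60%/80% of patients: (a) after 30% attrition about 55/83/110 are analysable, power is 51.5%/69.3%/81.4% two-sided or 64.2%/79.6%/88.8% one-sided, and the difference detectable with 90% power is 3.2/2.6/2.3 days two-sided or 2.9/2.4/2.05 days one-sided; (b) with no loss about 79/119/158 are analysable and power is 67.3%/84.2%/92.9% two-sided or 78.0%/90.7%/96.3% one-sided.*

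List the assumptions given in the verdict beside it. Make this section and Statistical Methods state the same sidedness. Interpret a non-significant primary result against these figures and the confidence interval.

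The cost is one rewritten paragraph and a less favourable power statement. No additional enrolment is asked for.

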### Data Collection Methods

Demographic data and data relating to symptomatic IrAEs and their management for both control and intervention groups are collected through EHR review of the clinical oncologist’s follow-up notes at each scheduled appointment with participants. Data from the EHR are recorded in REDCap electronic case report forms hosted in the server of the study sponsor’s Clinical Research Center [51]. PRO data are collected through the Kaiku Health electronic app, which contains 3 questionnaires. The questionnaires were selected by the study’s subinvestigator team, including a patient advocate ([name]), by discussing matters of burden and of pertinence of the collected data to patients, and what data were actionable for the model of care.

HRQoL data are collected via version 4 of FACT-G questionnaire, translated in French [46,52]. The questionnaire targets 4 domains: physical well-being, social or family well-being, emotional well-being, and functional well-being. Recall period, instrument scaling, scoring, and methods to handle missing data do not differ from the official administration and scoring guidelines [53]. The self-efficacy for managing symptoms is assessed weekly using the 8-item short-form French version of the PROMIS Self-Efficacy for Managing Chronic Conditions–Manage Symptoms measure [54]. Instrument scaling, scoring, and missing data handling also do not differ from the official scoring manual [55].

Symptom data in the intervention group are collected using a weekly PRO-CTCAE that includes symptom terms categorized as of the highest importance to monitor during ICI treatment. Thirty of the 37 symptom terms were identified through the Delphi study conducted in the first phase of the IePRO project [41]. The remaining 7 were selected by the IePRO project’s clinical team and principal investigators. All PRO-CTCAE items were translated in French. Currently, no official guidelines exist on how to best analyze PRO-CTCAE data longitudinally [56]. In this RCT, we will follow guidance provided by Basch et al [49] to calculate a single composite numerical grade for PRO-CTCAE symptom terms to facilitate longitudinal analysis.

As previously stated, active symptoms are reassessed daily during the first 3 months of the RCT. This is done by modifying the standard PRO-CTCAE recall period from 7 days to 24 hours. Although modifications to the recall period of PRO-CTCAE items are not encouraged, this is specifically due to potential considerable measurement errors, as that period is extended [57]. Recent studies [58,59] have highlighted how PRO measures using 24-hour recall periods more accurately convey symptom burden and variability over a short period of time, particularly for symptoms such as constipation, diarrhea, nausea, and those related to the patient’s emotional state. In patients treated with chemotherapy, shortened recall periods across different symptom PRO measures have enabled detection of clinically meaningful changes and were shown to be capable of detecting severe symptoms earlier [58,59]. Because some IrAEs can be fulminant and evolve in severity very quickly, daily reassessment of active symptoms could also support early detection and management. Although there is concern that the inclusion of all PRO-CTCAE items for daily assessment can be burdensome to patients, this concern addressed static questionnaires. In this intervention, questionnaires are dynamic and only active symptoms are reassessed daily to avoid overburdening patients.

To minimize missing data, the app requires respondents to provide a response before they are able to progress within the questionnaire. Patients receive automated reminders to reply to the questionnaires via email. In the event of early study discontinuation or withdrawal, all data collections, including PRO data, are halted. A semistructured interview guide based on the mHealth App Usability Questionnaire by Zhou et al [60] was developed to assess the usability of the ePRO app. Acceptability of the model of care will be assessed using an interview guide developed around the 7 constructs of acceptability of health care interventions as described by Sekhon et al [61]. Patient and individual staff interview data will be collected via audio recordings. Recordings will be transferred from the recording device’s secure digital card to be stored in the corresponding site’s local secured servers. Transcriptions of the recordings will be independently analyzed by 2 subinvestigators by using thematic analysis.

### Statistical Methods

In this RCT, the null hypothesis postulates that there is no difference in the primary end point (delay between symptom onset and detection be clinical team) between the intervention and control groups. The primary outcome will be analyzed comparing groups by means of multivariable regressions, adjusting for cancer type, age, and treatment regimen, against a 1-sided hypothesis. Secondary outcomes will be analyzed using multivariate regression analysis, controlled for cancer type, treatment regimen, and age. All statistical analyses will be presented as effect measure plus 95% CI, using a significance level of 5%. Variations in HRQoL and self-efficacy scores will be assessed by adjusting to baseline measure. Overall survival at 6 months will be controlled for cancer type and stage. All data processing and statistical analyses will be performed in R statistical software (v4.2.2; R Core Team 2023) and Microsoft Excel for Microsoft 365 MSO (version 2302, 2023). In-questionnaire data completeness is compulsory, though potential errors in the app may nevertheless occur. In addition, data such as time points may prove difficult to collect. According to the type and amount of missing data, strategies including imputation methods, deletions, or dismissals will be considered. For the HRQoL and self-efficacy for managing symptoms questionnaires, missing data will be handled according to official guidelines [53,55]. For exploratory outcomes, descriptive statistics will be applied. Qualitative data of semistructured interviews will be analyzed by the subinvestigators. Interviews will be transcribed verbatim and analyzed through thematic analysis.

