### Study Objectives and Outcomes

#### Primary Objective and Primary Outcome

The primary objective of the IePRO RCT is to compare the effect of an ePRO-based model of care to the current standard model of care on the delay between symptomatic IrAE onset and its detection by health care providers in patients with cancer treated with ICIs. The ePRO-based model of care complements the standard model of care with remote symptom monitoring via ePROs and remote symptom management via telephone triage calls done by oncology nurses. The primary outcome is the time-to-detection of IrAEs, as evidenced by a statistically significantly lower length of time when compared to that in usual care. Time to detection is the difference expressed in days between the IrAE detection date by the clinical team and the associated symptom’s onset date according to the patient’s self-report.

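### The primary test is 1-sided at 5%, but the 95% CI it is reported with and the 138-patient calculation both fit a two-sided 5% rule, so a result can be significant while its CI includes zero

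*Protocol article*

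**What the plan says.** Four places in the protocol article bear on the decision rule for the primary outcome.

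- **Statistical Methods, the test.** The null is that "the null hypothesis postulates that there is no difference in the primary end point" between the groups. The comparison is a multivariable regression "adjusting for cancer type, age, and treatment regimen, against a 1-sided hypothesis".
- **Statistical Methods, level and interval.** One rule covers primary and secondary outcomes alike: "All statistical analyses will be presented as effect measure plus 95% CI, using a significance level of 5" percent. No separate level, 1-sided bound or 90% CI is given for the primary outcome.
- **Primary Objective and Primary Outcome.** Success is directional: time to detection is to be shorter, "as evidenced by a statistically significantly lower length of time when compared to that in usual care".
- **Sample Size Calculation.** "A 2-sample *t* test with a statistical power of 90% and significance level set at .05 determined that 138 participants would be required". The effect sought is 2 days, with the SD of 3.65 days taken from the pilot records. Sidedness is not stated. Allowing for 30% attrition, the target becomes 198.

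**The concern.** The test, the interval and the sample size should express one decision rule. A 1-sided test at 5% agrees with a 90% two-sided CI or a 1-sided 95% bound. It does not agree with a two-sided 95% CI. If the CI is the usual two-sided one, the primary result can be declared positive while the interval printed beside it includes no effect.

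The sample size matters because it shows which rule the trial was designed around. If 138 comes from a two-sided 5% calculation, the trial was sized for a 2.5% chance of a false claim of benefit but will be judged at 5%. A reader who sees a significance level of .05 and 90% power in the design, and a 95% CI in the results, would not expect the looser threshold.

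**Working it through.** **Inputs.** Difference δ = 2 days, SD σ = 3.65 days, power 90%, significance level .05, total 138 and attrition 30% (Sample Size Calculation). Allocation is 1:1 (Study Design), so 69 per arm.

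**Step 1: attrition.** 138 / (1 − 0.30) = 197.1, rounded up to 198. This matches the stated target.

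**Step 2: which sidedness gives 138?** The normal approximation per arm is n = 2(z_α + z_power)²σ²/δ².

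- Two-sided 5%: 2 × (1.960 + 1.282)² × 3.65² / 2² = 69.99, so 70 per arm, 140 in total.
- 1-sided 5%: 2 × (1.645 + 1.282)² × 3.65² / 2² = 57.05, so 58 per arm, 116 in total.

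The exact calculation with the noncentral t distribution gives 71 per arm (142) two-sided and 58 per arm (116) 1-sided. The stated 138 is within 3% of the two-sided figures and far from 116. Cutting 69.99 down to 69 per arm would give exactly 138, though the article does not say how it rounded.

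**Step 3: power at 69 per arm.**

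| Test | Normal | Exact t |
|---|---|---|
| Two-sided 5% (or 1-sided 2.5%) | 89.6% | 89.2% |
| 1-sided 5% | 94.2% | 94.0% |

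The stated 90% fits the first row.

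**Step 4: where test and CI disagree.** For the unadjusted comparison, SE = 3.65 × √(2/69) = 0.621 days.

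- The 1-sided 5% test is significant from 1.645 × 0.621 = 1.02 days (1.03 with the t critical value on 136 degrees of freedom).
- The two-sided 95% CI excludes zero from 1.960 × 0.621 = 1.22 days (1.23 with t).

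Observed reductions between about 1.03 and 1.23 days, that is 1-sided p between 0.025 and 0.05, are therefore significant while the 95% CI includes zero.

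**Step 5: how often.** Under the null, the chance of landing in that zone is 5% − 2.5% = 2.5%. Under a true 2-day difference it is about 94.2% − 89.6% = 4.6% (normal approximation).

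**Step 6: size of the mismatch.** The chance of a false claim of benefit is 5% under the test as written, and 2.5% under the two-sided rule that fits the CI and the 138.

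**The case against.** Much of the case for the plan stands.

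- **The test does not exceed its own level.** A 1-sided test declared at 5% has a 5% type I error. A reader might infer that the false-positive rate is inflated. It is not: the factor of two holds only against the 2.5% implied by the CI and the sample size.
- **A 1-sided test is not wrong in itself.** The primary outcome is worded directionally, the direction is set in advance, and the trial is labelled phase II, where a prespecified 1-sided 5% test can be acceptable.
- **Two-sidedness is inferred.** Neither the CI nor the sample size is called two-sided, and a 2-sample test is not the same thing as a two-sided one. A 1-sided 95% bound would agree with the test. The reply is that an unqualified 95% CI, applied to all analyses, is conventionally read as two-sided, and that a 1-sided 5% calculation does not give 138.
- **Other features of the article are not evidence of error.** A null of no difference is compatible with a 1-sided alternative. Secondary outcomes worded in both directions do not contradict a directional primary, because the article attaches the 1-sided test only to the primary outcome. The surveillance bias that the Discussion acknowledges would shift the estimate, and a stricter critical value neither removes nor addresses it.
- **Sizing for a stricter test is harmless.** If the 1-sided 5% test is kept, the trial simply has about 94% power.
- **The zone of disagreement is narrow,** and the CI would be in view for readers to judge.

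What remains is that the article fixes sidedness, level and interval in the same paragraph, and on their ordinary reading they do not fit one another or the sample size.

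**Conclusion.** The point holds as an inconsistency between the test, the CI and the sample size. It is not a finding that the primary test is invalid or that its error rate exceeds what is declared. It should be fixed, but it does not undermine the design.

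In size, it is a 5% against a 2.5% chance of falsely claiming benefit, and a band of observed reductions about 0.2 days wide (1.23 − 1.03) in which the significance statement and the CI conflict. The article does not say how such a result would be read.

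The conclusion rests on the conventional two-sided reading of the 95% CI and on two-sided 5% being the origin of 138, which the recalculation supports but the article does not state. The figures in days assume 69 evaluable patients per arm, SD 3.65 and no covariate adjustment. Adjustment would change the SE and so move the band, but not the 2.5% against 5% mismatch.

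**What to change.** In Statistical Methods, specify for the primary outcome a two-sided 5% test, or equivalently a 1-sided test at 2.5%, so that it matches the 95% CI. In Sample Size Calculation, state that alpha is two-sided and that 138 evaluable participants give about 89% power for a 2-day difference. Record the change before the data are analysed, so that the choice cannot appear to depend on the result.

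The cost is a stricter threshold, with power of about 89% instead of 94%. A strict 90% two-sided would need 140 to 142 participants, or 200 to 203 after 30% attrition. The gap from 198 is too small to justify changing the target.

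An alternative is to keep the 1-sided 5% test, justify it, and report a 90% CI or a 1-sided 95% bound for the primary outcome. That aligns test and interval, but the sample size statement would then need correcting too: 116 evaluable (166 after attrition) for 90% power, or about 94% power at 138. The two-sided option fits what the article already reports with the least change.
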